## Abstract

**Background:**

The treatment of posttraumatic stress disorder (PTSD) related to a history of sexual and/or physical abuse in childhood is the subject of international debate, with some favouring a phase-based approach as their preferred treatment, while others argue for immediate trauma-focused treatment. A history of (chronic) traumatisation during childhood has been linked to the development of distinct symptoms that are often labelled as symptoms of complex PTSD. Many therapists associate the presence of symptoms of complex PTSD with a less favourable treatment prognosis. The purpose of this study is to determine whether a phase-based approach is more effective than stand-alone trauma-focused therapy in individuals with PTSD and possible symptoms of complex PTSD resulting from a history of repeated sexual and/or physical abuse in childhood. An additional aim is to investigate moderators, predictors of treatment (non) response and drop-out.

**Method:**

The sample consists of patients between 18 and 65 years old with a diagnosis of PTSD who report a history of repeated sexual and/or physical abuse in childhood (*N* = 122). Patients will be blindly allocated to either 16 sessions of eye movement desensitization and reprocessing (EMDR) therapy preceded by a stabilization phase (eight sessions of Skills Training in Affect and Interpersonal Regulation (STAIR)) or only 16 sessions of EMDR therapy. Assessments are carried out pre-treatment, after every eighth session, post-treatment, and at 3 and 6 months follow up. The main parameter will be the severity of PTSD symptoms (PTSD Symptoms Scale-Self Report). Secondary outcome variables are the presence of a PTSD diagnosis (Clinician-Administered PTSD Scale for DSM-5), severity of complex PTSD symptoms (Structured Interview for Disorders of Extreme Stress-Revised and symptoms-specific questionnaires), changes in symptoms of general psychopathology (Brief Symptom Inventory), and quality of life (Euroqol-5D). Health care consumption and productivity loss in patients will also be indexed.

**Discussion:**

The study results may help to inform the ongoing debate about whether a phase-based approach has added value over immediate trauma-focused therapy in patients suffering from PTSD due to childhood abuse. Furthermore, the results will contribute to knowledge about the safety, efficacy, and cost-effectiveness of treatments in this target group.

**Trial registration:**

Nederlands Trialregister, NTR5991. Registered on 23 august 2016. http://www.trialregister.nl/trialreg/admin/rctview.asp?TC=5991

**Electronic supplementary material:**

The online version of this article (10.1186/s13063-018-2508-8) contains supplementary material, which is available to authorized users.

## Background

For posttraumatic stress disorder (PTSD), international expert consensus guidelines recommend the use of evidence-based, trauma-focused psychological treatments, particularly cognitive behavioural therapy (i.e., prolonged exposure) and eye movement desensitization and reprocessing (EMDR) therapy [1, 2]. For PTSD following childhood abuse, the application of trauma-focused treatments is generally associated with reductions in PTSD symptom severity and comorbid symptoms of depression, anxiety, and dissociation [3–7].

Childhood physical and/or sexual abuse is considered to be one of the traumatic stressors associated with the development of complex PTSD [8]. The term complex PTSD was first launched by Herman [9] and is assumed to develop following the experience of severe, prolonged, and/or repeated interpersonal trauma. Complex PTSD is diagnosed when, in addition to meeting criteria for PTSD, trauma survivors exhibit disturbances in three domains of self-organization - affect regulation, self-concept, and interpersonal functioning [10] - and is currently being considered for inclusion as a separate diagnostic entity in *International Classification of Diseases 11* (ICD-11) [11].

It has been argued that individuals with a history of childhood abuse who suffer from symptoms of complex PTSD may be insufficiently stable to tolerate evidence-based immediate trauma-focused treatment [8, 12]. In 2011 the International Society for Traumatic Stress Studies (ISTSS) Complex Trauma Task Force published the results of a survey meant to obtain expert opinions about the treatment of patients with symptoms of complex PTSD [13] showing that 85% of the experts reported that they would use a phase-based approach as their first line of treatment. Based upon these results, a phase-based treatment has been recommended for these patients [8], in which trauma-focused treatment (phase II) is preceded by a stabilization phase (phase I) aimed at ensuring the individual’s safety, reducing self-regulatory problems, and improving emotional, social, and other psychological skills. This phase-based approach is then completed with a reintegration phase (phase III), aimed at consolidating treatment gains and helping the person to adapt to his or her present life circumstances [8]. In clinical practice, the phase I treatment for PTSD with symptoms of complex PTSD varies from eight weekly sessions (i.e., the programme Skills Training in Affective and Interpersonal Regulation (STAIR)) [14] up to programme with a much longer duration [15, 16]. In the guidelines of the ISTSS the majority of the experts considered 6 months as a reasonable length for phase I [8].

Until now, the safety and efficacy of the phase-based treatment approach for treating complex PTSD has been addressed in two studies [12, 14]. The first study used a randomized controlled trial (RCT) to compare the efficacy of STAIR (a phase I treatment) followed by prolonged exposure versus a waiting-list condition in a sample of female patients that suffer from PTSD as a result of childhood physical and/or sexual abuse [14]. The STAIR/exposure condition resulted in significant symptom reductions (i.e., PTSD severity, depression, general anxiety, dissociation), plus significant improvements in mood and anger regulation skills. In the STAIR phase, depression, anxiety, anger expression, and negative mood regulation improved significantly. There were no improvements in PTSD symptoms, dissociation, and alexithymia. The prolonged Exposure (PE) phase showed reductions in PTSD symptoms, dissociation, and alexithymia, and further improvements in depression and anxiety. No improvements were found in negative mood regulation and in anger expression in the PE phase. The results of this study suggest that the combination of STAIR/exposure is feasible and leads to a decrease in PTSD and a broad range of other symptoms associated with complex PTSD. One limitation of this study, however, was the relatively high drop-out rate in the STAIR/exposure condition (29% compared to 11% in the waiting list control group). Also, effect sizes pointed to the phase of exposure treatment conferring the bulk of the therapeutic benefits. Hence, although this study supports the effectiveness of a STAIR/exposure combination, the results do not provide univocal support for the contention that a phase-based treatment is superior to immediate trauma-focused treatment for individuals suffering from severe PTSD and symptoms of complex PTSD (see also [17]). Clearly, there was a need for direct comparison between a phase-based and an immediate trauma-focused treatment condition. Accordingly, in a second study, Cloitre and colleagues evaluated the efficacy of a phase-based treatment (STAIR/exposure) versus supportive counselling followed by prolonged exposure (support/ exposure) and versus STAIR followed by supportive counselling (STAIR/support) [12]. Women with PTSD related to childhood sexual and/or physical abuse were assigned to one of the three treatment conditions. The application of STAIR/exposure was found to be associated with greater benefits compared to the support/exposure condition in terms of self-reported reduction in PTSD symptom severity, interpersonal problems, and emotion regulation, but only at follow up (both 3 and 6 months). Immediately after treatment, all three experimental treatment conditions resulted in a substantial proportion of patients being PTSD negative (i.e., no significant differences were found between the three conditions). However, the lack of a treatment condition in which patients were directly exposed to their traumatic memories precludes drawing any firm conclusions about the relative benefits of a phase-based treatment approach over an immediate trauma-focused approach for patients suffering from PTSD related to childhood abuse (see De Jongh et al.) [18]. In other words, the core question is still whether the addition of a stabilization phase is a necessary condition for, and/or has added value over, immediate trauma-focused treatment. And if so, it is important to know which of the two treatment approaches works best for whom. The present study aims to address these questions.

## Methods/design

### Aim

The purpose of the current study “ToPrepareOrNot” (TOPRON), is to determine whether a phase-based approach is more effective than immediate trauma-focused treatment in individuals with PTSD related to repeated childhood abuse, and possible symptoms of complex PTSD. For the trauma-focused condition we used eye movement desensitization and reprocessing (EMDR) therapy, because it is one of the guideline treatments for PTSD [2] with an efficacy similar to PE. Our first hypotheses is based upon the current guidelines for the treatment of complex PTSD [8], and expert consensus about the treatment of this target population [13]; that is, that the phase-based treatment condition (i.e., STAIR/EMDR) is significantly more effective in PTSD (severity of PTSD symptoms and proportion of diagnoses lost) than the immediate trauma-focused condition (i.e., EMDR/EMDR). Our second hypothesis is that the phase-based treatment approach leads to a significantly better outcome in terms of reduced symptoms of complex PTSD and comorbid symptoms, drop-out rate, quality of life, and health care consumption than the immediate trauma-focused condition. An additional aim is to investigate potential moderators and predictors of drop-out or treatment (non) response. To this end, we hypothesized that signs of affect dysregulation and having interpersonal problems at the start of therapy would be related to worse outcome in the trauma-focused condition [19, 20]. We also expect patients with a comorbid personality disorder [21] and high level of dissociation at the start of therapy [22] to be more at risk of deterioration and drop-out in both conditions.

### Study design

The TOPRON study entails a randomized controlled trial with two arms: a phase-based treatment approach (STAIR-EMDR) versus a trauma-focused treatment condition (EMDR therapy only). In the STAIR-EMDR condition, patients will receive eight sessions of stabilization treatment (STAIR), followed by 16 sessions of EMDR therapy, adding up to a total number of 24 treatment sessions. In the trauma-focused condition, patients will receive 16 sessions of EMDR therapy. All sessions last 90 min. The two groups will be compared on a number of variables before treatment, after every eighth session, post-treatment and at follow up, that is 3 months and 6 months after the post-treatment session (see Figs. 1 and 2). By assessing every eight sessions it will be possible to determine the added value of a stabilization phase examining the results after an equal amount of sessions. For this study, we chose to use a fixed number of sessions. All patients in the STAIR-EMDR condition will receive eight sessions STAIR while in both conditions patients will receive a maximum of 16 sessions of EMDR. When all targets are processed to a Subjective Unit of Distress (SUD) score of 0 and a Validity of Cognition (VoC) score of 7, the patient will be assessed to determine whether he or she no longer meets the criteria for PTSD. In the case of early completion, the remaining sessions are cancelled. Because STAIR is meant as a first-phase treatment prior to the start of trauma-focused treatment (i.e., EMDR therapy) following STAIR, all patients will receive EMDR therapy. That is the reason that early completion during STAIR is not possible.

**Fig. 1 Fig1:**
[figure not shown]
Study design, showing treatment conditions and measurements. BDI-II, Beck Depression Inventory; BSI, Brief Symptom Inventory; CAPS, Clinician-Administered PTSD Scale for DSM-5; DERS, Difficulties in Emotion Regulation Scale; DES-II, Dissociative Experiences Scale; EMDR, Eye Movement Desensitization and Reprocessing; EQ-5D, Euroqol-5D; IIP, Inventory of Interpersonal Problems; LEC-5, Life Events Checklist for DSM-5; PSS-SR, PTSD Symptoms Scale-Self Report; PTCI, Posttraumatic Cognitions Inventory; SCID-II, Structured Clinical Interview for DSM-IV Axis II; SIDES-R, Structured Interview for Disorders of Extreme Stress-Revised; STAIR, Skills Training in Affect and Interpersonal regulation; T, time point; FU, follow up

**Fig. 2 Fig2:**
[figure not shown]
Enrolment, treatment and assessments over time. BDI-II, Beck Depression Inventory; BSI, Brief Symptom Inventory; CAPS, Clinician-Administered PTSD Scale for DSM-5; DERS, Difficulties in Emotion Regulation Scale; DES-II, Dissociative Experiences Scale; EMDR, Eye Movement Desensitization and Reprocessing; EQ-5D, Euroqol-5D; IIP, Inventory of Interpersonal Problems; LEC-5, Life Events Checklist for DSM-5; PSS-SR, PTSD Symptoms Scale-Self Report; PTCI, Posttraumatic Cognitions Inventory; SCID-II, Structured Clinical Interview for DSM-IV Axis II; SIDES-R, Structured Interview for Disorders of Extreme Stress-Revised; STAIR, Skills Training in Affect and Interpersonal regulation; *t*, time point; FU, follow up

### Research setting

Patients will be recruited from various departments of Dimence, a large mental health organization in the east of the Netherlands. Dimence specialises in treating patients with severe mental illnesses.

### Participants

The inclusion criteria are (a) age between 18 and 65 years, (b) diagnosis of PTSD according to the *Diagnostic and Statistical Manual of Mental Disorders 5* (DSM-5) [23], and (c) victim of repeated sexual and/or physical abuse before the age of 18 years by a carer or a person in a position of authority (i.e., with repeated abuse defined as more than one incident by the same or different perpetrator(s)). The exclusion criteria are (a) insufficient proficiency in the Dutch language, (b) high risk of suicidality assessed by the Beck Depression Inventory (BDI)-II [24]), (c) treatment for PTSD in the past year with at least eight sessions (EMDR, prolonged exposure, or any well-evaluated stabilization programme), (d) alcohol or drug dependence or abuse according to DSM-IV-TR [25], (e) mental retardation, and (f) victim of ongoing physical and/or sexual abuse.

### Interventions

STAIR [14] will be applied In the first treatment phase (phase I, stabilization). The goals of this treatment are (a) addressing problems in affect and interpersonal regulation and (b) preparing the individual for the effective and successful use of the trauma-focused treatment [14]. The programme consists of eight sessions with different topics (introduction, emotional awareness, emotion regulation, emotionally engaged living, understanding relationship patterns, changing relationship patterns, agency in relationships, and flexibility in relationships). All STAIR sessions have more or less an identical format and structure: psycho-education about the rationale and goals of the interventions, skills acquisition, skills application, and practice. The therapeutic techniques employed include for example identifying and exploring cognitive schemes, role-playing, behavioural exercises at home, and respiration exercises.

The trauma-focused element in therapy will be EMDR therapy, which is a protocolised evidence-based trauma treatment, aimed at resolving symptoms as a result of disturbing or unprocessed life experiences [26]. The treatment starts with recalling the traumatic memory and selecting the most distressing part of this memory with associated dysfunctional thoughts and feelings about oneself. Whilst concentrating on the traumatic memory, the patient is asked to follow the therapists’ fingers with his/her eyes, while being encouraged to follow every association that comes up in the patient’s mind. Repeatedly the patient is asked to report the experiences that come up, which may be cognitive, emotional, somatic, or imaginary. After some sets of eye movements, the patient is asked to report a SUD between 0 and 10, until the disturbance related to the memory reaches a SUD of zero and positive beliefs about oneself related to the trauma are rated as feeling true on a VoC scale of 1–7. Like previous studies [27], we removed stabilization elements (e.g., establishing a “safe place”) from the EMDR standard protocol to avoid interference with the stabilization condition to assure absolute distinction between the two conditions. Like STAIR, the EMDR therapy will be offered twice a week in this study.

All participating therapists hold a post-Master’s psychology degree, have completed STAIR training and advanced training in EMDR therapy, and will provide therapy in both treatment conditions. They will be supervised by experienced trainers who were trained by the originators of both treatment protocols (i.e., Shapiro and Cloitre). Adherence to treatment will be encouraged in several ways. Prior to the start of treatment, a supervised case-conceptualisation will be made in order to plan the treatment sessions. Furthermore, the therapists will be asked to fill out protocol-specific checklists and to explicitly report and explain deviations from the treatment protocol after each session. In addition, all treatment sessions will be recorded on video and a random selection of these recordings will be evaluated during monthly group supervision meetings (one hour for EMDR therapy and one hour for STAIR). Additional supervision will be provided via e-mail and telephone upon request from the therapist. Ultimately, a random selection of individual therapy sessions (33%) will be rated for adherence by two trained psychology graduates using both EMDR and STAIR specific fidelity checklists.

### Procedures

During the regular intake procedure conducted by a clinician not involved in this study and without influence on assignment to the conditions, patients with PTSD due to repeated sexual and/or physical abuse during childhood will be asked to participate in the study. After their approval by signing an informed consent form, they will be assessed on the inclusion and exclusion criteria.

After assessment for eligibility (T0) and baseline assessment (T1; see Fig. 1), the patients will be randomly assigned to one of the two conditions. The randomization will be executed by a computerized randomization programme [28], creating a list of randomized assignment per location (strata). Randomization blocks of six or eight will be employed (divided over four strata based on treatment location) and generated by a study-independent collaborator. The assignments will be put into envelopes per location and will be picked for each patient in order from top to bottom as listed by the computerized randomization. Within each randomly assigned condition, the participants will be assigned to one of the therapists, based on availability. During treatment, assessments will take place after every eight sessions, post-treatment, and at 3 and 6 months follow up.

Due to the nature of the trial, participants and clinicians in the study cannot be blinded to treatment assignment. The research assistants (students studying for a Master’s degree in psychology) who will carry out the assessments will receive intensive training on the interviews and do not have any interest in the outcomes of this study.

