### Power and sample size calculation

To our knowledge, methods for power calculation in the context of linear mixed models are unavailable. A power calculation based on repeated measures analysis of variance (ANOVA) was therefore used as a conservative approximation, with treatment condition as the between-subjects factor and time as the within-subjects factor. For 2 × 5 (between-subjects (treatment condition) × within (pre-treatment, after every eight sessions, post-treatment, 3 month follow up and 6 month follow up) repeated measures ANOVA (alpha 0.05, power 0.80, correlation between measures 0.5, and small effect-size (*f)* 0.10), a total sample size of 122 subjects will be required (*G* power) [60].

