### Data analysis

Descriptive analyses will be used to evaluate demographic, clinical and baseline characteristics of both treatment arms. Analyses will be performed on the intent-to-treat basis and the sample of completers: the data of all randomized participants will be analysed using both groups as defined at randomization. On the continuous outcome measures, the groups will be compared using linear mixed models. Baseline scores will be included as covariates, time as a categorical variable, and treatment condition as a fixed effect.

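### Randomisation is stratified by four treatment locations, but the listed model terms omit location, so standard errors for single-time-point contrasts may be slightly too large

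*Protocol article*

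**What the plan says.** The Procedures section of the protocol article describes randomisation by a computer programme "creating a list of randomized assignment per location (strata"), and continues: "Randomization blocks of six or eight will be employed (divided over four strata based on treatment location"). Location is the only stratification factor named.

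The Data analysis section states the model class, "On the continuous outcome measures, the groups will be compared using linear mixed models", and then the terms: "Baseline scores will be included as covariates, time as a categorical variable, and treatment condition as a fixed effect". Location is not among them. The Power and sample size calculation section does not use it either; there the design is two conditions by five measurements. No random effect is described, not even one for patient.

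On therapists, Procedures says: "Within each randomly assigned condition, the participants will be assigned to one of the therapists, based on availability". Interventions adds that they "will provide therapy in both treatment conditions".

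**The concern.** When treatment is balanced by permuted blocks inside each location, differences between locations largely cancel from the comparison of arms. The sampling variance of the treatment estimate then reflects only variation within locations. A model without location does not know this. It counts differences between locations as unexplained variation between patients and reports a standard error for a less precise design than the one actually run. A patient random effect or a general covariance matrix over time does not help, because the location variance is simply absorbed into the between-patient part.

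What is at stake is modest: confidence intervals a little too wide, a test a little below its nominal level, and some power given away. It concerns the comparisons of arms at particular assessments, and the Discussion section gives weight to those at post-treatment and follow-up.

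**Working it through.** **Inputs from the article.** Four location strata with blocks of six or eight (Procedures). Model terms: baseline, time, treatment (Data analysis). "alpha 0.05, power 0.80, correlation between measures 0.5, and small effect-size" *f* of 0.10, five measurements, total N of 122 (Power and sample size calculation).

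**Assumptions.** Allocation is 1:1, which is not stated but fits two arms and even block sizes. The share *v* of residual variance lying between locations after baseline adjustment is not given; 2%, 5% and 10% are used as a range.

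**Step 1: the plan's own figure.** For the treatment-by-time interaction in a 2 × 5 repeated measures ANOVA, the noncentrality is λ = f²·N·m/(1 − ρ) = 0.01 × 122 × 5/0.5 = 12.2, with 4 and (122 − 2) × 4 = 480 degrees of freedom. Power is 0.805. At N = 120 it is 0.798, so 122 is the smallest even N reaching 0.80 and the stated figure reproduces. A location effect that is constant over time cancels from this within-patient test, so omitting or adding location does not change N = 122.

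**Step 2: standard error of a contrast at one time point.** With blocking within location, the true variance is proportional to 1 − v, while the model without location reports one proportional to 1. The reported standard error is therefore too wide by the factor r = 1/√(1 − v).

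**Step 3: actual test level.** The test rejects when the estimate exceeds 1.960·r true standard errors, so α = 2·[1 − Φ(1.960·r)].

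**Step 4: power.** Take as reference an effect detected with 80% power when location is in the model, that is, 1.960 + 0.842 = 2.802 true standard errors. Only the reported standard error is inflated, so power = Φ(2.802 − 1.960·r). Dividing the whole 2.802 by r would be wrong here: it would put back location variance that the blocking has already removed.

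| Assumed v | r | 1.960·r | Actual α | Power |
|---|---|---|---|---|
| 2% | 1.010 | 1.980 | 0.048 | Φ(0.822) = 79.4% |
| 5% | 1.026 | 2.011 | 0.044 | Φ(0.791) = 78.5% |
| 10% | 1.054 | 2.066 | 0.039 | Φ(0.736) = 76.9% |

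**Step 5: simulation check.** 4,000 trials per setting were simulated with N = 122, four locations, blocks of six or eight, one endpoint and no treatment effect. The Monte Carlo standard error is √(0.05 × 0.95/4000) = 0.34 percentage points. Type I error without and with location in the model was 5.0% and 5.1% at a location share of 2%, 4.4% and 4.8% at 5%, and 4.3% and 5.1% at 10%. At 10%, the mean reported standard error was 0.179 against an actual spread of 0.171.

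The direction agrees with the formula. The size is a little smaller because four location effects are drawn afresh each time, and on average only three quarters of their variance appears within a trial. The expected share is then 0.075/0.975 = 7.7%, giving r = 1.041 and α = 0.041. At 2% the effect is too small for the simulation to detect.

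**The case against.** The strongest objection is that the article is condensed. Its Data analysis section is a few sentences long, and a full analysis plan may well name location. This stands as a limit on how hard the point can be pressed. It does not remove it, because the article lists the fixed terms and the one factor the design stratifies on is not there.

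Second, the loss may be negligible. What matters is the variance left after baseline adjustment, and the sites are departments of one organisation (Research setting), so the low end of the range may be the realistic one. That stands. The error is also conservative: the test level falls below 5%, not above it.

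Third, 80% power is a reference value here. The plan claims it for the interaction test, not for a contrast at a single time point. That also stands, so the power column shows relative loss only.

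A reader might go further and infer that leaving out therapist makes the primary standard errors too small. The documents do not support this. Therapist is not a stratification factor, and therapists work in both arms, so a therapist main effect does not inflate error: simulated type I error without location in the model was 4.9% and 4.3% at therapist shares of 5% and 10%, with a location share of 5%. Only a treatment effect that differs between therapists inflates it. With 20 therapists (assumed; no number is given), a variance of that effect of 0.05 or 0.10 relative to total variance gave 5.7% or 6.6%. Adding location did not remove this (6.0% and 6.8%). Nothing in the article indicates such heterogeneity, and common training, supervision and fidelity checks work against it. As no random-effects structure is described at all, the absence of therapist cannot be read as a decision to exclude it.

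**Conclusion.** The point holds for location and is small. The listed model does not match the stratified design. If location is prognostic after baseline adjustment, the reported standard errors for between-arm contrasts at a given time point are about 1% to 5% too wide, and 0.6 to 3.1 percentage points of power are lost from 80%, for an assumed residual location share of 2% to 10%. If location is not prognostic, the loss is zero.

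It would be wrong to infer that the treatment estimate is biased, that 122 patients are too few for the test they were sized for, or that false positives become more likely through the omission of location. None of these follows. The therapist reading is not upheld.

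**What to change.** In the Data analysis section, add location (four levels) as a fixed effect to the linear mixed models that compare the arms. This costs three degrees of freedom out of roughly 120 and one sentence of text. Every patient's location is already known, because it determined which randomisation list was used. N = 122 stays as it is.

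A therapist-by-treatment random effect may be added as a sensitivity analysis only. The article does not list therapist among the recorded variables, so this would need confirming. The variance would also be poorly estimated: with an assumed 10 to 30 therapists, each therapist-by-arm cell would hold about 122/20 = 6 down to 122/60 = 2 patients.
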